## Abstract

**Objectives:**

Stroke is the second leading cause of death and the third leading cause of disability among non-communicable diseases globally. The prevalence, incidence, and mortality rates of stroke are higher in high-altitude regions compared to lowland areas. However, compared to plain areas, the efficacy of endovascular therapy for large vessel occlusive acute ischemic stroke (LVO-AIS) in high-altitude regions remains unclear.

**Methods and Design:**

This study is a multicenter, prospective, endpoint-blinded cohort study. From January 2025 to December 2027, a total of 1,052 patients with acute large vessel occlusion ischemic stroke (LVO-AIS) from the Western Sichuan Plateau will be prospectively enrolled, including those who receive endovascular treatment and those who do not. Baseline characteristics and endovascular treatment details will be documented. Treatment decisions are guided by clinical practice guidelines, taking into account high-altitude real-world constraints such as patient or proxy refusal and delays in interhospital transfer. Medical records will be established for each patient, and a 180-day follow-up will be conducted. The primary outcome was the proportion of patients achieving functional independence [modified Rankin scale (mRS) range from 0 to 2] at 90 days. The secondary outcomes included the mRS score at 90 days, early neurological improvement rate [defined as a National Institutes of Health Stroke Scale (NIHSS) score of 0–2 or a reduction of ≥8 points from baseline within 24 h of enrollment], changes in NIHSS scores between day 7 ± 1 or discharge and baseline, quality of life as assessed by the five-level EuroQol five-dimensional questionnaire at 90 days, and cognitive function at 180 days will be assessed using mini-mental state examination and montreal cognitive assessment scores. Imaging outcomes will include the rate of successful reperfusion (defined as a modified Thrombolysis in Cerebral Infarction score ≥2b) and infarct volume measured within 5–7 days. Statistical analysis and fused optimized multimodal learning were blinded to the group assignments.

**Conclusion:**

This study aims to evaluate the efficacy of endovascular treatment compared with standard medical therapy in patients with LVO-AIS in the Western Sichuan Plateau and to develop an artificial intelligence–based prognostic model to refine treatment strategies for this and other high-altitude regions.

**Clinical trial registration:**

https://www.chictr.org.cn/showproj.html?proj=241870, ChiCTR2400092762.

## 1 Introduction

Stroke is a leading cause of death and disability globally, with large vessel occlusive acute ischemic stroke (LVO-AIS) posing a serious threat to health burden due to its high rates of disability and mortality. LVO-AIS (1) is a critical medical emergency characterized by acute occlusion of major cerebral arteries, such as the internal carotid artery or middle cerebral artery, leading to local cerebral ischemia and hypoxia which result in extensive cerebral infarction and severe disability or death if blood flow is not restored promptly. With the advancement of medical technologies, endovascular treatment (EVT) has become a crucial therapeutic approach for LVO-AIS, marking a new era in the treatment of ischemic penumbra by combining imaging techniques to identify low perfusion areas. It significantly improves reperfusion rates and enhances patients' neurological outcomes particularly when administered within 6 h of onset (2). The time window for thrombectomy in anterior circulation large vessel occlusion has now been extended to 24 h (3, 4). The Basilar Artery Occlusion Chinese Endovascular Trial (BAOCHE) (5) and Trial of Endovascular Treatment of Acute Basilar-Artery Occlusion (ATTENTION) (6) has confirmed the superiority of thrombectomy in the posterior circulation within 24 h.

An increasing number of individuals are engaging in tourism and recreational activities in high-altitude regions. Additionally, certain groups—including military personnel, miners, tour guides, and local residents—are chronically exposed to such environments. A global survey in 2021 estimated that approximately 500 million people reside at altitudes of ≥1,500 m (7), with China possessing the world's largest plateau region, home to roughly 12 million permanent residents (8). Notably, our previous literature review demonstrated that patients with ischemic stroke in high-altitude areas have significantly poorer functional outcomes compared with those in low-altitude regions. Moreover, differences in infarct localization have been observed, with anterior circulation strokes being more prevalent, and, according to TOAST classification, a higher incidence of large-artery atherosclerosis (9). These findings underscore the need for high-quality research to better inform clinical decision-making for ischemic stroke in high-altitude populations.

In the Western Sichuan Plateau, due to its unique geographical and climatic conditions, the incidence and mortality rates of stroke may be higher than in lowland areas, potentially linked to factors such as the hypoxic environment, cold climate, and lifestyle habits of the residents. Our previous meta-analysis (10) showed that the stroke prevalence is higher in high-altitude regions, with variations observed across different sampling types and geographical locations. Age, female gender, hypertension, and obesity are identified as potential risk factors in this population. However, it remains unclear whether patients with AIS in high-altitude areas benefit from EVT.

In recent years, the rapid development of machine learning is expected to enhance the predictive accuracy of the prognosis for certain treatment methods. The key advantage of the fused optimized multimodal learning model lies in its ability to handle imbalanced information across modalities. Progressive fusion effectively retains fine-grained information from earlier layers by gradually integrating features, while avoiding the information loss and feature conflicts that often arise in traditional early fusion methods (11). Orthogonal sequential fusion sequentially weights each modality's data, reducing inter-modal interference and ensuring the independence and diversity of each modality (12). Balanced multimodal learning dynamically adjusts the learning strategies for each modality, addressing the challenge of uneven contributions and improving the model's performance in complex multi-task learning scenarios (13). Together, these methods optimize the model's robustness in the presence of data imbalance, noise interference, and high-dimensional feature spaces, making it particularly suitable for high-complexity tasks such as medical imaging and genomics data analysis.

This study aims to prospectively collect data from LVO-AIS patients in the Western Sichuan Plateau to explore the efficacy of EVT in this population, providing evidence for endovascular interventions for AIS patients in the region. Furthermore, after validating the effectiveness of EVT for LVO-AIS in the Western Sichuan Plateau, an artificial intelligence-based prognostic prediction model will be developed using relevant data, significantly facilitating the treatment of AIS patients in this region.

## 2 Methods

### 2.1 Study design

This is a multicenter, prospective, endpoint-blinded study aimed at evaluating the efficacy of EVT in patients with LVO-AIS from the Western Sichuan Plateau, in comparison with standard medical treatment (SMT). We prospectively enroll LVO-AIS patients from this region who receive either EVT or SMT, collect baseline characteristics and EVT-related data, and conduct univariate and multivariate analyses to explore associated factors. As a prospective observational study, the exposure is not subject to artificial assignment or manipulation between the EVT and non-EVT groups. The follow-up period is standardized to 180 ± 7 days. Patients who failed to complete the follow-up were excluded to ensure data integrity. The detailed procedure is illustrated in Figure 1.

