### 2.2 Sample size estimation and participants

We estimated that group sample sizes of 526 in each group will achieve 90.031% power to detect a difference between the group proportions of functional independence [modified Rankin scale (mRS) range from 0 to 2] at 90 days of 0.135. According to the Multicenter Randomized CLinical trial of Endovascular treatment for Acute ischemic stroke in the Netherlands (MR CLEAN) (14) trial, the proportion in control group is assumed to be 0.191 under the null hypothesis and 0.326 under the alternative hypothesis. The significance level of the test is 0.05. Considering a 20% dropout rate, the final sample sizes for both groups were 526. Given the large data requirements of machine learning, we doubled the sample size of each group based on the original estimates.

A total of 1,052 patients with acute large vessel occlusion stroke were enrolled from Ya'an People's Hospital, Ganzi Tibetan Autonomous Prefecture People's Hospital, and Liangshan Yi Autonomous Prefecture First People's Hospital (Figure 2), including both those who underwent endovascular treatment and those who did not. Although all patients met the current guideline-based indications for mechanical thrombectomy, some did not receive the procedure due to various factors, such as declining treatment over concerns about surgical risk or experiencing delays in transfer to thrombectomy-capable centers. In this study, these branch centers primarily served as referral sites or admitted patients who declined endovascular therapy. All participating centers implemented a standardized, homogeneous protocol for medical management. Prior to group assignment, patients who met the criteria for intravenous thrombolysis and had no contraindications were eligible to receive intravenous thrombolysis.

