### 2.3 Outcomes

The primary outcome is the proportion of patients achieving functional independence (mRS 0–2) at 90 days post-stroke. The secondary outcomes are divided into clinical efficacy outcomes and imaging markers. The clinical efficacy outcomes include: (1) mRS score at 90 days; (2) early neurological improvement rate (defined as NIHSS score of 0–2 or a reduction of ≥8 points from baseline within 24 h of enrollment); (3) changes in NIHSS scores between day 7 ± 1 or discharge and baseline; (4) Quality of life assessed by five-level EuroQol five-dimensional questionnaire (EQ-5D-5L) at 90 days, and (5) Montreal cognitive assessment (MOCA) and mini-mental state examination (MMSE) scores at 180 days. The imaging endpoints include: (1) reperfusion rate [modified thrombolysis in cerebral infarction (mTICI) ≥ 2b on DSA] and (2) infarct volume based on diffusion-weighted MRI within 5–7 days. All data will be collected through electronic media and uploaded in real-time to a centralized data management platform for storage.

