### 2.4 Statistical analysis

Statistical analyses will be conducted using R version 4.3.3 by an independent statistician blinded to group assignments. Continuous variables will be tested for normality using the Shapiro–Wilk test (α = 0.05). Normally distributed data will be presented as means ± standard deviations and compared using the independent *t*-test or one-way analysis of variance. Non-normally distributed data will be presented as medians with interquartile ranges and compared using the Wilcoxon rank-sum test or Kruskal–Wallis test. Categorical variables will be summarized as counts and percentages, with group comparisons performed using the χ^2^ test or Fisher's exact test.

Given the non-randomized allocation of treatment (EVT vs. SMT), potential confounding by indication will be addressed using propensity score methods. A logistic regression model including baseline covariates (age, sex, baseline NIHSS, onset-to-enrollment time, comorbidities, and relevant imaging findings) will be used to estimate the propensity score for receiving EVT. We will perform both propensity score matching (1:1 nearest-neighbor without replacement, caliper = 0.2 SD of the logit) and inverse probability of treatment weighting (IPTW) to adjust for baseline imbalances. Standardized mean differences (SMDs) will be reported to assess covariate balance before and after adjustment.

Primary analyses will be performed on the matched cohort, with IPTW analyses conducted as sensitivity analyses. Logistic regression will be used for binary outcomes, linear regression for continuous outcomes, and ordinal logistic regression for ordinal outcomes, all adjusted for residual imbalances after matching. Results will be reported as adjusted odds ratios (aOR) with 95% confidence intervals (CIs).

To address missing data, multiple imputation using chained equations (MICE) will be employed under the missing-at-random assumption, generating 20 imputed datasets. Analyses will be conducted on each dataset, and results will be pooled using Rubin's rules. Sensitivity analyses will compare complete-case and imputed results to assess robustness.

All hypothesis tests will be two-sided, with *p* ≤ 0.05 considered statistically significant. No interim analyses are planned.

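### Excluding patients who do not complete 180-day follow-up drops observed 90-day primary outcomes and removes the patients whom the imputation plan should cover

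*Protocol article*

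**What the plan says.** Section 2.1 of the Protocol article fixes the length of follow-up: "The follow-up period is standardized to 180 ± 7 days". The next sentence sets the rule at issue: "Patients who failed to complete the follow-up were excluded to ensure data integrity".

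Section 2.3 places the main endpoint earlier: "The primary outcome is the proportion of patients achieving functional independence (mRS 0–2) at 90 days post-stroke". The only outcomes it lists at the end of follow-up are secondary: "Montreal cognitive assessment (MOCA) and mini-mental state examination (MMSE) scores at 180 days".

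Section 2.4 describes a different approach to incomplete data: "To address missing data, multiple imputation using chained equations (MICE) will be employed under the missing-at-random assumption, generating 20 imputed datasets". It adds: "Sensitivity analyses will compare complete-case and imputed results to assess robustness".

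Section 2.2 budgets for loss: "Considering a 20% dropout rate, the final sample sizes for both groups were 526". The Discussion accepts that some loss to follow-up will occur. Section 2.2 refers the detailed exclusion and withdrawal criteria to an Appendix that is not among the documents at hand.

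**The concern.** The rule in section 2.1 is tied to the end of a 180-day follow-up, but the primary endpoint is complete at day 90. Nothing in the text limits the rule to the 180-day outcomes or to patients without a 90-day mRS. A patient seen at day 90 and lost afterwards has a known primary outcome and is still excluded.

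The rule also runs against section 2.4. The main candidates for outcome imputation are patients lost to follow-up, and they are removed before imputation starts. Two statisticians working from this text could build different primary analysis sets.

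The possible harm is bias. Completing follow-up happens after treatment and may depend on both treatment group and outcome. The propensity model in section 2.4 uses baseline covariates only, so neither matching nor weighting can in general repair selection on a later event. Different loss by group is plausible here. Section 2.2 says that untreated patients include those who refused the procedure or were delayed in transfer, and that the branch centers mainly referred patients or admitted those who declined.

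**Working it through.** **Inputs from the Protocol article.** Section 2.2: independence 0.191 (control) and 0.326 (EVT), difference 0.135, alpha 0.05, 20% dropout, doubling for machine learning, 526 per group, 1,052 in total. Section 2.4: two-sided tests.

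**The plan's own figure.** With pooled variance under the null and 90% power, the mean rate is 0.2585 and

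n = [1.960·√(2·0.2585·0.7415) + 1.282·√(0.191·0.809 + 0.326·0.674)]² / 0.135² ≈ 219 per group.

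Then 219 × 1.2 = 262.8, rounded up to 263, and 263 × 2 = 526. The stated size reproduces.

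**How many patients the rule could touch.** At the planned 20%, 0.20 × 526 ≈ 105 per group, or 0.20 × 1,052 ≈ 210 in all, leaving about 421 per group. This is the dropout allowance applied to everyone. It does not estimate how many excluded patients would have a known 90-day mRS, which the documents do not allow one to work out.

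**Planned contrast.** Difference 0.326 − 0.191 = 0.135. OR = (0.326/0.674)/(0.191/0.809) = 2.05.

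**Illustration 1: outcome-related loss in one group (assumed).** Each group loses 20%. In one group, 10% of independent patients are lost; in the other group, loss is unrelated to outcome.

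- SMT affected: dependent patients lost = (0.20 − 0.10·0.191)/0.809 = 22.4%. Observed SMT rate = 0.191·0.90/0.80 = 0.215. Difference = 0.326 − 0.215 = 0.111.
- EVT affected: dependent patients lost = (0.20 − 0.10·0.326)/0.674 = 24.8%. Observed EVT rate = 0.326·0.90/0.80 = 0.367. Difference = 0.367 − 0.191 = 0.176.

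**Illustration 2: deaths treated as non-completers (assumed).** The documents give no death rate. If a fraction d of a group dies and is dropped, and none of those patients was independent at day 90, the observed rate is p/(1 − d).

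| Deaths dropped, SMT / EVT | Observed rates | Difference | OR |
|---|---|---|---|
| none | 0.191 / 0.326 | 0.135 | 2.05 |
| 30% / 20% | 0.273 / 0.4075 | 0.135 | 1.83 |
| 20% / 20% | 0.239 / 0.4075 | 0.169 | 2.19 |
| 30% / 10% | 0.273 / 0.362 | 0.089 | 1.51 |
| 10% / 20% | 0.212 / 0.4075 | 0.195 | 2.55 |

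In the 30%/20% row the difference stays at 13.5 points and only the OR moves. Both scales matter: section 2.2 plans on the difference and section 2.4 reports adjusted odds ratios.

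With no true effect (0.191 in both groups), dropping 20% SMT and 10% EVT deaths gives rates of 0.239 and 0.212, OR 0.86. The reverse pattern gives OR 1.16.

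**Power.** At 421 per group, unmatched, the same normal approximation gives 99.5%. Loss of power is not the issue.

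**The case against.** The strongest defence is that sections 2.1 and 2.4 can be read together. The imputation text speaks of missing data in general. Among patients who complete follow-up, baseline covariates for the propensity model can be missing, and so can single visits such as the 24-hour NIHSS, infarct volume or EQ-5D-5L. A reader might infer that the two sections are logically incompatible, or that the complete-case analysis must equal the main analysis. Neither follows: any missing covariate among completers makes the two analyses differ. The objection stands to that extent. It does not rescue the rule, because the document nowhere says that imputation is confined in this way, and the reading still discards observed 90-day outcomes.

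A reader might also infer that the plan removes deaths. The text shown does not say so. Failing to complete follow-up usually means loss or withdrawal, the Discussion treats the matter as loss to follow-up, and the withdrawal criteria are in the unseen Appendix. The deaths point is therefore a question to settle and not an established error.

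Finally, a reader might infer a known bias from the figures above. The loss patterns and death rates are assumed, and one of the death scenarios leaves the risk difference unchanged. The figures show that the estimate can move, and in either direction; they do not show that it will, or by how much. An unseen analysis plan might define the analysis set properly, but the sentence in section 2.1 would still have to be corrected, because it is a stated rule and not a missing detail.

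**Conclusion.** The point holds for the rule as written. Completion of 180-day follow-up decides who enters a 90-day primary analysis. It discards observed primary outcomes and leaves the imputation and the complete-case comparison to act only on covariates or single visits missing among completers. This is selection on a post-treatment event that baseline propensity scores cannot correct, and it should be fixed before analysis.

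Confidence is high on the mismatch of time points and on the need to reconcile sections 2.1 and 2.4. The size and direction of any bias are unknown. Under the assumed one-sided, outcome-related loss, the planned 13.5 points become 11.1 or 17.6. The effect of dropping deaths applies only if deaths are treated as non-completion: over assumed death rates of 10–30% (SMT) and 10–20% (EVT), the planned OR of 2.05 would lie between 1.51 and 2.55.

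**What to change.** Delete the exclusion sentence in section 2.1, or narrow it so that 180-day completeness governs only the 180-day outcomes. State that the primary analysis:

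- includes all enrolled eligible patients, whether or not they complete follow-up;
- uses every 90-day mRS obtained in its window, regardless of day-180 status;
- counts deaths by day 90 as mRS 6, that is, not functionally independent;
- applies the planned imputation to 90-day outcomes that are truly missing, with the complete-case analysis kept as the planned sensitivity analysis.

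State explicitly that death is not failure to complete follow-up, and check that the Appendix agrees.

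The cost is a wording change and minor programming, with no new data. The small downside is that, for patients lost before day 90, the primary result will rest on imputation under missing-at-random.

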**Figure 1 F1:**
[figure not shown]
Research workflow diagram. NIHSS, National Institutes of Health Stroke Scale; CT, computed tomograph; MRI, magnetic resonance imaging; mRS, modified rankin scale; TOAST, trial of org 10,172 in acute stroke treatment; EQ-5D-5L, five-level EuroQol five-dimensional questionnaire; MOCA, montreal cognitive assessment; MMSE, mini-mental state examination.

This study has been prospectively registered with the Chinese Clinical Trial Registry [registration number ChiCTR2400092762 (https://www.chictr.org.cn/showproj.html?proj=24187)], and it has been approved by the Ethics Committee of Ya'an People's Hospital (approval No. 2024045).

### 2.2 Sample size estimation and participants

We estimated that group sample sizes of 526 in each group will achieve 90.031% power to detect a difference between the group proportions of functional independence [modified Rankin scale (mRS) range from 0 to 2] at 90 days of 0.135. According to the Multicenter Randomized CLinical trial of Endovascular treatment for Acute ischemic stroke in the Netherlands (MR CLEAN) (14) trial, the proportion in control group is assumed to be 0.191 under the null hypothesis and 0.326 under the alternative hypothesis. The significance level of the test is 0.05. Considering a 20% dropout rate, the final sample sizes for both groups were 526. Given the large data requirements of machine learning, we doubled the sample size of each group based on the original estimates.

A total of 1,052 patients with acute large vessel occlusion stroke were enrolled from Ya'an People's Hospital, Ganzi Tibetan Autonomous Prefecture People's Hospital, and Liangshan Yi Autonomous Prefecture First People's Hospital (Figure 2), including both those who underwent endovascular treatment and those who did not. Although all patients met the current guideline-based indications for mechanical thrombectomy, some did not receive the procedure due to various factors, such as declining treatment over concerns about surgical risk or experiencing delays in transfer to thrombectomy-capable centers. In this study, these branch centers primarily served as referral sites or admitted patients who declined endovascular therapy. All participating centers implemented a standardized, homogeneous protocol for medical management. Prior to group assignment, patients who met the criteria for intravenous thrombolysis and had no contraindications were eligible to receive intravenous thrombolysis.

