**Figure 2 F2:**
[figure not shown]
Recruitment coverage for study participants.

The inclusion criteria encompass: (1) aged above 18 years; (2) resides in a high-altitude region of Western Sichuan (with an altitude above 1,500 meters); (3) clinically diagnosed with AIS and confirmed by computed tomography angiography (CTA) or digital substraction angiography (DSA) to have large vessel occlusion; (4) The interval between last known well and enrollment will be within 24 h, and (5) signed informed consent and able to comply with follow-up requirements. The main exclusion criteria mainly include: (1) Pre-onset mRS score > 2; (2) computed tomography (CT) or magnetic resonance imaging (MRI) confirms the presence of intracranial hemorrhage or the infarct size exceeds one-third of the supply area of the middle cerebral artery; (3) History, previous imaging, or clinical judgment suggests the presence of a brain tumor, arteriovenous malformation, or intracranial artery dissection, or (4) History of head trauma within the past 3 months. Detailed exclusion and withdrawal criteria are provided in Appendix.

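### Groups follow the treatment received while enrolment is not tied to a step in care before transfer, so events after eligibility can decide the group, and matching on the named covariates cannot be relied on to correct this

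*Protocol article*

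**What the plan says.** Section 2.1 (Study design) enrols patients who receive either EVT or SMT and states that exposure is not assigned. Section 2.2 explains how eligible patients reach the SMT group: "some did not receive the procedure due to various factors, such as declining treatment over concerns about surgical risk or experiencing delays in transfer" to a centre able to perform thrombectomy. The Abstract gives the same two reasons. Section 2.2 adds that the branch centres mainly refer patients or admit those who decline, and that thrombolysis may precede group assignment. It does not define the moment of assignment.

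The only timing rule at entry is in the inclusion list of section 2.2: "The interval between last known well and enrollment will be within 24 h". Occlusion may be confirmed by CTA or DSA.

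Section 2.4 builds the propensity score from age, sex, baseline NIHSS, "onset-to-enrollment time", comorbidities and imaging findings. The primary analysis uses the 1:1 matched cohort, and IPTW is a sensitivity analysis.

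On comparability, section 2.2 opens a sentence with "Although all patients met the current guideline-based indications for mechanical thrombectomy". None of the five inclusion criteria states this requirement.

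**The concern.** In a comparison of treatments received, the group should be fixed, and baseline measured, at one moment that precedes whatever decides treatment. Here a transfer can lie between eligibility and treatment, and its success helps to decide the group. A patient intended for EVT who arrives too late joins SMT; one whose transfer succeeds joins EVT. If the two kinds of patient differ in prognosis, the groups differ even when EVT has no effect.

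Because branch centres mainly refer patients or keep those who decline, the place of enrolment may track the treatment group. NIHSS and imaging could then be pre-transfer values for many SMT patients and post-transfer values for many EVT patients. Matching on them would pair patients who look alike at different stages of the pathway. Early neurological improvement, which section 2.3 counts from enrolment, has the same weakness. At stake is whether the primary odds ratio can be read as an effect of EVT.

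**Working it through.** **1. The plan's own figure.** Section 2.2 says "the proportion in control group is assumed to be 0.191 under the null hypothesis and 0.326 under the alternative hypothesis", a difference "at 90 days of 0.135", and "The significance level of the test is 0.05"; section 2.4 makes tests two-sided. For 90% power with pooled variance:

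n = [1.960 × √(2 × 0.2585 × 0.7415) + 1.282 × √(0.191 × 0.809 + 0.326 × 0.674)]² / 0.135² = 219 per group.

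219 × 1.2 = 263 and 263 × 2 = 526, which reproduces the stated size. The sentence "group sample sizes of 526 in each group will achieve 90.031% power" does not reproduce: power is 90.0% at 219 and 99.9% at 526. That is a separate matter. It is relevant here because a study this large will often declare a modest spurious difference significant.

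**2. What the text fixes and leaves open.**

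| Item | Where | Status |
|---|---|---|
| Group | 2.1, 2.2 | treatment received; transfer delay leads to SMT |
| Enrolment | 2.2, inclusion list | within 24 h of last known well; no step in care named |
| Occlusion confirmed | 2.2, inclusion list | CTA or DSA, so possibly at different stages |
| Group assignment | 2.2 | after any thrombolysis; moment not defined |
| Propensity covariates | 2.4 | centre and transfer status not named |
| Primary outcome | 2.3 | 90 days after stroke in both groups |

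**3. Illustration of size (assumed inputs).** The documents give neither the share of SMT patients who failed transfer (f) nor their independence rate (r). Assume no EVT effect, 526 per group, an independence rate of 0.191 both in the whole intended-EVT pool and in the other SMT patients, and no adjustment:

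- EVT observed = 0.191(1 + f) − r·f
- SMT observed = f·r + 0.191(1 − f)
- Difference = 2f(0.191 − r)

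| f | r | EVT | SMT | Difference | Chance of significance in that direction |
|---|---|---|---|---|---|
| 0.10 | 0.15 | 0.195 | 0.187 | +0.008 | 5% |
| 0.20 | 0.10 | 0.209 | 0.173 | +0.036 | 32% |
| 0.20 | 0.05 | 0.219 | 0.163 | +0.056 | 64% |
| 0.40 | 0.05 | 0.247 | 0.135 | +0.113 | 99.7% |
| 0.10 | 0.35 | 0.175 | 0.207 | −0.032 | 26% |
| 0.20 | 0.35 | 0.159 | 0.223 | −0.064 | 75% |

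The sign depends only on whether r lies below or above 0.191. The two kinds of patient can also offset each other. If f = 0.20 with r = 0.10, a further share of SMT who improved before EVT cancels the bias at 0.20 × 0.091 / 0.159 = 11% (their rate 0.35) or 0.20 × 0.091 / 0.309 = 6% (their rate 0.50).

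**4. Eligibility statement.** The inclusion list requires age, residence, confirmed occlusion, 24 h and consent with follow-up. The exclusions shown (pre-onset mRS above 2, haemorrhage, large infarct and others) cover thrombectomy indications only in part. The Appendix is described as holding detailed exclusion and withdrawal criteria, so it is not an evident place for a positive entry requirement.

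**The case against.** A reader might infer that there is no common time zero, that this is established immortal-time bias, and that EVT is favoured. The documents do not support that.

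- **Clocks.** Last known well and enrolment apply to both groups, the primary outcome runs from stroke in both, and time from onset to enrolment is in the propensity model. What stands is narrower: enrolment is not attached to a common step in care.
- **Direction.** No passage says that patients worsen in transit or are moved to SMT after worsening. Patients who recanalise after thrombolysis, or milder patients who refuse, would push against EVT.
- **Adjustment.** If NIHSS and imaging were taken after deterioration, matching would capture part of it. Patients with haemorrhage, an infarct over the size limit, or more than 24 h elapsed might never be enrolled. Both arguments depend on when enrolment happens, which is the open point.
- **Size.** The figures above model the crude contrast, not the matched analysis. Scenarios in which every failed transfer does badly give a large share of the planned 13.5 points by construction.
- **Condensation.** Figure 1 and the Appendix are not shown, and the full protocol may fix the enrolment point. The article nevertheless states the grouping by treatment received and the covariate list, and those together create the problem.

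**Conclusion.** The point holds in this form. Grouping by treatment received, with delayed transfers counted as SMT, lets events after eligibility decide the group. The covariates meant to correct for this are taken at a point not anchored before transfer, and centre and transfer status are not named among them, so matching cannot be relied on to remove the selection bias. It would favour EVT if failed-transfer patients do worse than the rest, and would work against EVT if they do better.

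Neither sign nor size follows from the documents. The range shown, about −6 to +11 points, rests on assumed shares and rates, no true effect and no adjustment; it shows sensitivity and is not an estimate of bias in the planned analysis. Separately, the statement that all patients met thrombectomy indications is not carried by the inclusion list, and the two must be reconciled.

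**What to change.** 1. Define time zero for both groups as the first assessment at any participating hospital at which study eligibility is met, before transfer or the EVT procedure. It should not be the DSA in the EVT centre, which for transferred patients comes after the event that helps to decide the group. State in advance how patients whose occlusion is first confirmed by DSA are handled.
2. Take NIHSS, imaging and time from onset for the propensity model from that point.
3. Record there whether the guideline indication is met and which treatment strategy is intended.
4. Reconcile the eligibility statement in section 2.2 with the inclusion list.
5. Add a sensitivity analysis grouping patients by intended strategy at time zero, with failed transfers kept in the intended-EVT group.

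Cost: one or two extra items at first presentation, one extra analysis, and possibly some patients leaving the primary set once the eligibility text is reconciled. The documents do not say that intent is already recorded, and it is hard to reconstruct later, so the change should be made early. It alters no patient's care.
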